## Methods and statistical analysis

### Design

This study has a mixed factorial-experimental nested design. In total, each couple engages four times in the emotional sharing task, twice in the co-rumination and twice in the natural sharing condition. Each participant will twice share a distressing experience and will twice act as supporter. Both aspects will be experimentally manipulated between participants. Measures of mood and appraisal will be nested within participants, while movement and cardiovascular synchrony will be nested within dyads. The chronic variables (i.e., dyadic coping and relationship variables) will be used correlational.

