### Co-rumination manipulation

We will experimentally manipulate the instructions of the emotional sharing task, following a validated procedure developed by Tudder et al (2023) [27]. For half of the sharing episodes, the supporter will receive instructions that promote co-rumination, which involves focusing on a topic, repeatedly discussing the issues, speculating about the antecedents and consequences of the issues, and exploring and unearthing negative emotions. For the other sharing episodes, the supporter will be instructed to respond in a natural way to the sharer. The order of the co-rumination versus natural response will be counterbalanced. Each member of the couple will be instructed once to engage in co-rumination and once to engage naturally with the sharer in all four conditions, the participants will receive digital instructions and physical cards to remind them of their role and the associated instructions.

Before the first sharing episode, participants will be taken by their experimenter to the emotional sharing space with the two armchairs (see Fig 1b), so that they can familiarize themselves with this space Then they will be taken back to their private space, where they will be informed about the first experience to address and be asked to “collect their thoughts” for two minutes. Following this, each participant will again be taken to the emotional sharing space. Participants will then engage in their first round of emotional sharing on the selected experience. After completing the first emotional sharing episode, the participants will go back to the private space and complete the post-dialogue survey about their sharing experience. After completing the first instruction, the instructions for natural sharing and co-rumination will be reversed, and after two rounds, the roles of the sharer and supporter will be switched, and vice versa.

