Specifically, in each 8-minute dialogue, the motion energies of both participants will be cross-correlated in non-overlapping window segments of 30 seconds. The choice of a 30-second window size (750 frames) is to account for the shorter turn-taking latencies in question-centered discussions, consistent with previous work [30]. Windowed cross lagged cross-correlation of up to 5 seconds of positive and negative time lags will be computed with a step size of 0.1 seconds, achieved by progressively shifting one time series relative to the other [9]. The resulting matrix of cross-correlations will then be transformed using Fisher’s r-to-Z transformation, and their absolute values will be aggregated over the entire 8-minute interval of the dialogue, resulting in a shared global value of nonverbal synchrony for every sharing episode [9].

To ascertain whether the synchrony detected via MEA exceeded what might occur by chance (i.e., pseudosynchrony), we will engage a specific RMEA function designed for generating pseudointeractions through automated surrogate algorithms. This function shuffles the days in the data and calculates all possible motion energy interactions between couples in the dataset. Subsequently, it dissociates the original pairings, followed by the extraction of a predefined amount of unique MEA datasets, each selected just once to avoid duplication.

To test Hypothesis 1, we will examine whether relationship partners show greater synchrony than pseudo-dyads during the emotional sharing tasks. Following recommendations by Helm et al. (2018) [31] and DiGiovanni et al. (2024) [18], we will compute windowed cross-correlations to generate time series of movement synchrony. We will then apply multilevel modeling (MLM) using the *lme4* package in R to compare synchrony scores between real dyads and matched pseudo-dyads, accounting for the nested structure of time windows within dyads. To test Hypothesis 2, we will examine whether co-rumination leads to greater synchrony than natural sharing. Movement synchrony data will be modeled using multilevel models with time windows (Level 1) nested within participants (Level 2) and dyads (Level 3). Experimental condition (co-rumination vs. natural sharing) will be entered as a fixed effect predictor, and dyad ID and participant ID will be modeled as random effects. This approach accounts for both the repeated nature of the synchrony time series and the interdependence between partners in a dyad.

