To assess whether cardiovascular synchrony exceeds what would be expected by chance (i.e., pseudosynchrony), we will follow the approach of Feldman et al. (2011) [34] and more recent adaptations by DiGiovanni et al. (2024) [18]. We will first calculate windowed cross-correlations on the interbeat interval (IBI) time series for each dyad during the interaction, using time-lagged windows to account for dynamic shifts in coupling. To test whether the observed synchrony exceeds random coupling, we will generate a surrogate dataset of randomly paired pseudo-dyads, and then use multilevel modeling (MLM) to compare synchrony scores between real and pseudo-dyads. This model will account for the nested structure of time windows within dyads and the repeated nature of physiological data. To test Hypothesis 2, we will use MLM to compare cardiovascular synchrony between the co-rumination and natural sharing conditions, including condition as a fixed effect and random intercepts for dyad and participant where appropriate. This approach allows us to properly model interdependence between partners and repeated time-based observations within each interaction episode.

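### The H2 model for movement synchrony has a participant level that a pair score lacks and no term for the episode, the unit given a condition, so its standard error is too small whenever synchrony varies between episodes

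*Protocol article*

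**What the plan says.** All places are in the protocol article.

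- **Outcome.** Under Phasic timescale, the motion series of both partners are cross-correlated in non-overlapping 30-second windows over each eight-minute dialogue and then aggregated, "resulting in a shared global value of nonverbal synchrony for every sharing episode". The Design section agrees: "movement and cardiovascular synchrony will be nested within dyads".
- **Condition.** Design: "each couple engages four times in the emotional sharing task, twice in the co-rumination and twice in the natural sharing condition". Co-rumination manipulation: "For half of the sharing episodes, the supporter will receive instructions that promote co-rumination". The latter section adds that each partner, when supporting, has one episode under each instruction.
- **Movement model for H2.** The levels are "time windows (Level 1) nested within participants (Level 2) and dyads (Level 3". The instruction given is the only fixed predictor named. On the random part, the article states that "dyad ID and participant ID will be modeled as random effects". No episode term is listed. The article says that this handles both the repeated series and the interdependence of partners.
- **Cardiovascular model for H2.** A multilevel model "including condition as a fixed effect and random intercepts for dyad and participant where appropriate". It has no episode term either.
- **Error rate.** Two-sided 0.05 with a Bonferroni correction, whose divisor is not stated (Chronic timescale).

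**The concern.** There are two structural faults.

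First, a cross-correlation between two partners belongs to the pair. Neither partner has a value of their own, so a participant level has no natural meaning. The article does not say how a pair score would be attached to a participant ID.

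Second, the comparison of interest is between episodes, because the instruction changes from one episode to the next. Without an episode term, windows from one conversation are treated as separate pieces of evidence about the instruction. Each partner writes down two experiences, so the four episodes cover four different topics, and the Discussion itself raises fatigue over four conversations. Some variation between episodes is therefore to be expected. The model would read such variation as more precise information on condition than the data hold.

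At stake is a hypothesis that Table 1 lists as confirmatory, on an outcome that the Abstract names as primary at the phasic timescale.

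**Working it through.** **The plan's own figure.** The only reproducible number nearby is the sample size. For an effect of 0.5, 80% power and two-sided 0.05, the t-based formula gives 63.77, so 64 per group and 128 in total, as stated. It does not bear on the H2 standard error. The figure in question is the two-sided 0.05.

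**Inputs from the article.** 150 dyads; 4 episodes per dyad, 2 per condition; 480 s / 30 s = 16 windows per episode. This gives 150 × 4 = 600 episodes and 600 × 16 = 9,600 windows, or 300 episodes and 4,800 windows per condition.

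**Assumed input.** ρ is the share of the variance remaining within participant that lies between episodes. The article gives no value, so a range is shown. Total within-participant variance is set to 1.

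**Can a participant intercept replace the episode term?** Take participant ID to be the episode's sharer, with one row per window. Each partner supports once under each condition, so each partner also shares once under each condition. The intercept then appears once on each side of the condition contrast and cancels. The same holds if the ID is the supporter. The variation between that person's two episodes is left unmodelled.

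**Closed form.**

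- True variance of the difference in condition means: 2 × (16ρ + 1 − ρ) / 4,800.
- Variance that the stated model reports: 2 × [(1 − ρ) + 16ρ × 299/9,299] / 4,800. Here 299 = 600 − 300 − 1 and 9,299 = 9,600 − 300 − 1, and 16 × 299/9,299 = 0.514.
- Ratio: R = (16ρ + 1 − ρ) / [(1 − ρ) + 0.514ρ].
- Type I error: 2 × [1 − Φ(1.96/√R)].

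Example at ρ = 0.10: R = 2.5/0.951 = 2.63, 1.96/√2.63 = 1.21, error 22.7%.

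Simulation used 3,000 trials per setting with no condition effect. The assumed dyad and participant variances, 0.30 and 0.05, cancel from the contrast.

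| ρ (assumed) | R | Closed form | Simulated, stated model | Simulated, episode as unit |
|---|---|---|---|---|
| 0 | 1.00 | 5.0% | 5.3% | 5.3% |
| 0.01 | 1.16 | 6.8% | 6.3% | 4.7% |
| 0.02 | 1.31 | 8.7% | 8.6% | 4.9% |
| 0.05 | 1.79 | 14.3% | 15.1% | 5.5% |
| 0.10 | 2.63 | 22.7% | 23.0% | 5.2% |
| 0.20 | 4.43 | 35.2% | 34.8% | 5.1% |
| 0.30 | 6.44 | 44.0% | 43.6% | 4.1% |

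The last column compares episode means within sharer, which in this balanced design corresponds to adding an episode intercept.

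**Checks.**

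- Fitted mixed models at ρ = 0.10 (8 data sets) gave a squared ratio of standard errors, with versus without an episode intercept, of 2.57, against R = 2.63.
- With 128 dyads and ρ = 0.10 the simulated error is 22.7%, so more couples do not remove the inflation.
- With ρ = 0 but an assumed correlation of 0.2 between successive windows, it is 11.0%.
- If each window score were entered once per partner, the reported variance would halve. Then R = 2 at ρ = 0 and the error is 2 × [1 − Φ(1.96/√2)] = 16.6% (simulated 15.6%).

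**Bonferroni.** With an assumed divisor of 8 (Table 1 has eight hypotheses), the threshold is 0.05/8 = 0.625%, z = 2.734. Replacing 1.96 by 2.734 gives 1.7%, 4.1%, 9.2% and 19.4% at ρ = 0.02, 0.05, 0.10 and 0.20. All are above 0.625%.

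**The case against.** The strongest reply is that the size of the problem is unknown. It depends on an episode variance share that the article does not give, and at 0 to 0.02 the unadjusted error is only about 5% to 9%. That stands. A reader might infer that type I error is far above 5% whatever the data look like; the document does not support this.

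A reader might also infer that a participant level forces every pair score to be entered twice. It does not. Coding the ID as sharer or supporter needs one row per window, and the article says nothing about duplicate rows. The figure of about 16% at zero episode variance is therefore conditional on a coding that is not stated.

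Third, the cardiovascular text is looser. Participant intercepts are used only where appropriate, and the text claims to handle repeated observations within each episode. This shows that clustering was in mind, but the only intercepts named are dyad and participant, so the omission remains. The figures above cannot be applied there: no window length is given, and the section also describes a zero-lag correlation.

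Fourth, the article already defines one value per episode, and analysing that value would avoid the inflation. But the H2 sentence names time windows as Level 1.

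Finally, this is a condensed article and H2 is worded cautiously. Neither answers the point, because the article itself states the levels, the fixed effect and the random effects.

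**Conclusion.** The concern holds for the structure of the movement-synchrony model. The participant level contradicts the article's own definition and nesting of the score. The unit that receives the condition has no term, and neither a participant intercept nor Bonferroni supplies one. As written, the standard error for the condition effect is too small whenever synchrony varies between episodes.

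The size is conditional on an assumed episode share, with one row per window and 16 windows per episode: close to nominal at 0, modest inflation at 0.01 to 0.02, and roughly three to seven times nominal at 0.05 to 0.20 before Bonferroni. For cardiovascular synchrony the same omission is present, but its size cannot be stated.

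**What to change.** For H2, drop the participant level for the pair score. Then do one of the following:

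- keep the windows and add a random intercept for episode within dyad, beside the dyad intercept; or
- analyse the single value per episode that the article already defines (150 × 4 = 600 rows) with a dyad random intercept.

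Apply the same change to cardiovascular synchrony. A dyad-level condition slope and fixed effects for episode position and for which partner shares are optional. If synchrony depends on who shares, that variance goes into the residual but cancels from the contrast, so leaving it out errs on the cautious side.

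The cost is a change of model formula and a wider confidence interval for the condition effect. No data collection changes.

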Compared to the effects of the co-rumination manipulation on synchrony, mood and appraisal change, we expect that couples’ relationship quality and their dyadic coping strategies have a much stronger effect on synchrony, mood and appraisal change. Couples with a high relationship quality and constructive dyadic coping strategies will already have employed a range of interpersonal emotion regulation and coping strategies to deal with the problem they are discussing, and therefore these brief episodes of natural sharing or co-rumination will minimally affect their synchrony, mood and appraisal changes. In contrast, for couples with a poorer relationship quality or dyadic coping strategies, the co-rumination manipulation to engage in extensively discussing the sharers problems and negative emotions, will have a greater effect on their synchrony and positive mood change than when they engage in their natural way of emotional sharing, but will still result in minimal appraisal changes.

Prior to the emotional sharing task, we will measure a set of variables related to the chronic timescale: relationship quality, dyadic coping and a range of secondary variables (e.g., attachment style, empathy and perceived social support). During the emotional sharing task itself, we will assess phasic processes in the form of movement synchrony [5] and cardiovascular synchrony [20]. Before and after the emotional sharing tasks, we will measure tonic processes: mood and appraisal changes and a range of secondary variables (e.g., conversation experience, perception of partners’ responsiveness and feelings of closeness with the partner).

The proposed experiment has both confirmatory and exploratory parts. The confirmatory part is based on hypotheses that were explicitly derived from the literature on interpersonal emotion regulation. Because of the complexity of the study, we have grouped our hypotheses according to their respective timescales (see Table 1). More detailed information can be found in *Supplementary 1 in*
S1 File*.*

**Table 1 pone.0323526.t001:** Main confirmatory hypotheses for the three timescales.

Timescale	Hypotheses
*Phasic*	1. Relationship partners will display significant levels of movement and cardiovascular synchrony during the emotional sharing tasks, relative to a relevant baseline level of randomized pseudo-interactions. 2. Compared to natural sharing, co-rumination may be associated with enhanced movement and cardiovascular synchrony.

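### The pseudo-dyads that define chance synchrony for H1 are not restricted to the role, instruction and dialogue position that every real pair shares, so the contrast can be biased either way.

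*Protocol article*

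**What the plan says.** Table 1 of the protocol article states H1 for both signals: partners show synchrony "relative to a relevant baseline level of randomized pseudo-interactions".

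The Phasic timescale part of the data analysis plan then describes the surrogates twice.

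- **Movement.** "This function shuffles the days in the data and calculates all possible motion energy interactions between couples in the dataset". Next, "it dissociates the original pairings, followed by the extraction of a predefined amount of unique MEA datasets". The model is then said to "compare synchrony scores between real dyads and matched pseudo-dyads". The matching variable is not named.
- **Cardiovascular.** "we will generate a surrogate dataset of randomly paired pseudo-dyads, and then use multilevel modeling (MLM) to compare synchrony scores between real and pseudo-dyads". Two published approaches are cited for the method. No restriction on the draw is stated.

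The real pairs have a fixed structure. Under Emotional sharing task, each of the four eight-minute dialogues has one sharer and one supporter. Under Co-rumination manipulation, each dialogue runs under one of two instructions, and their order is counterbalanced.

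**The concern.** A surrogate comparison isolates partner-specific coupling only if the pseudo-dyads keep everything else the real pairs have in common. Here that means one sharer with one supporter, the same instruction, and the same place in the session. Random re-pairing without restriction keeps none of these.

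Suppose heart rate or movement follows a time course typical of the first dialogue, of co-rumination, or of the supporter role. The difference between real and pseudo-dyads then mixes that time course with coupling between partners. H1 concerns only the coupling. It could be declared supported with no coupling present, or real coupling could be hidden because sharers and supporters respond differently. H1 is one of the confirmatory hypotheses, and the pseudo-dyads are its only reference level.

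**Working it through.** The plan gives no figure for this contrast, so there is none to reproduce.

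**Inputs from the protocol article:** 150 couples (Sample size determination); four eight-minute dialogues (Emotional sharing task); 2,000 ms epochs, then removal of a quadratic trend and ARIMA filtering (Cardiovascular measurement and synchrony); two-tailed 0.05 with Bonferroni (Chronic timescale).

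**Assumed, not in the document:** a correlation ρ that the task itself induces between two people's series, shown at 0.01 and 0.02; one pseudo-dyad per real pair; pseudo-partners drawn uniformly.

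**Step 1. What an unrestricted draw contains.** For one sharer's series, the other couples supply 149 × 4 × 2 = 1,192 series. A quarter are from the same position, half are from a supporter, and half are under the same instruction if the order is balanced evenly. All three agree in 1/4 × 1/2 × 1/2 = 1/16.

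**Step 2. Expected real-minus-pseudo difference with no partner coupling.**

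| Source of shared timing | Real | Unrestricted pseudo | Difference |
|---|---|---|---|
| Same in all dialogues and both roles | ρ | ρ | 0 |
| Specific to position | ρ | ρ/4 | +0.75ρ |
| Specific to instruction | ρ | ρ/2 | +0.5ρ |
| Opposed in sharer and supporter | −ρ | (ρ − ρ)/2 = 0 | −ρ |

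If pseudo-dyads are matched on role, instruction and position, the difference is 0 in every row. The last row assumes a correlation that keeps its sign. The planned movement score averages absolute values, so exactly opposed responses would look alike there.

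**Step 3. Precision.** Each dialogue has 480/2 = 240 epochs, and there are 150 × 4 = 600 dialogues. The SE of one correlation is about 1/√240 = 0.0645. For the mean it is 0.0645/√600 = 0.00264, and for the real-minus-pseudo difference √2 × 0.00264 = 0.00373.

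**Step 4. Rejection in the direction of the bias,** Φ(|difference|/0.00373 − 1.96), against a nominal 2.5% per side:

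| Source | ρ = 0.01 | ρ = 0.02 |
|---|---|---|
| Position | Φ(2.01 − 1.96) = 52% | Φ(4.02 − 1.96) = 98% |
| Instruction | Φ(1.34 − 1.96) = 27% | Φ(2.68 − 1.96) = 76% |
| Opposed roles (downward) | Φ(2.68 − 1.96) = 77% | Φ(5.37 − 1.96) > 99% |

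**Step 5. Simulation.** The set-up had 150 couples, 4 positions, 240 epochs, quadratic detrending, no partner coupling, and a t-test on couple means in place of the multilevel model. Position-specific timing gave false synchrony in 50% (ρ = 0.01) and 97% (ρ = 0.02). Opposed roles gave a false lower-than-chance result in 67% and 100%; a repeat of the 0.01 case gave 75%. Timing common to everything gave about 2–3% per side. Pairing on role and position stayed near nominal throughout.

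A separate simulation added AR(1) pre-whitening and 30-second windows and used a much larger shared signal. With timing specific to the dialogue, the real mean was 0.352 and the unrestricted pseudo mean 0.087, close to the quarter expected from Step 2. Rejection was 1.00 unrestricted and 0.015 within the same dialogue. With lagged absolute Fisher z, the form planned for movement, it was 1.00 and 0.05.

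**Step 6. Bonferroni.** The number of tests is not stated. If it were 20, the level would be 0.0025 and the critical value 3.02. The position row becomes Φ(2.01 − 3.02) = 16% and Φ(4.02 − 3.02) = 84%.

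**The case against.** The strongest reply is that random re-pairing is the usual control for shared timing. Timing common to every couple and dialogue appears equally in real and pseudo-dyads and cancels. That stands. A reader might infer that any task timing shared by all couples would pass as synchrony; Step 2 and the simulation show that it does not.

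A reader might also infer that movement has a stricter reference than heart rate because only the movement text says matched. The document does not support this. The movement surrogates are also built by shuffling and re-pairing, and Table 1 gives one randomised reference for both signals. The difference is mostly one of wording.

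Nor does the document say that the draw actually crosses roles, instructions or positions. Its wording permits this, but the cited approaches, not available here, may already restrict the draw, and an article can leave such detail to the full plan. This limits how firmly an error can be asserted. The article is not silent, however: it states the reference for a confirmatory hypothesis, and states it without restriction.

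Finally, the task-locked signal may be small. The dialogues are free conversation, no timed cue within a dialogue is described, order is counterbalanced, and detrending with ARIMA filtering removes slow shared trends. This bears on the size of ρ. Counterbalancing stops position and instruction from coinciding but does not remove timing specific to either. Detrending and pre-whitening did not remove the artefact in the simulation with the larger signal.

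**Conclusion.** The concern holds in a limited form. As written, the surrogate rule for both measures lets pseudo-dyads differ from real pairs in role, instruction and position. The H1 contrast can then move up or down without partner-specific coupling. The direction and the mismatch shares follow from the design and a uniform draw; the size does not, because ρ is an assumption. With 600 dialogues the contrast is precise enough for a position-specific ρ of 0.01 to 0.02 to give roughly 50% to 97% false positives at an unadjusted 0.05, fewer after Bonferroni. If ρ is zero, or the draw is already restricted, there is no bias. The simulations simplify the planned multilevel and ARIMA models. This is a worthwhile and cheap correction to a stated rule, not a demonstrated false result.

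**What to change.** For both measures, build each pseudo-dyad from the sharer of one couple and the supporter of a different couple, in the same instruction condition and the same dialogue position, with both series aligned from dialogue onset. State this in the cardiovascular text in place of random pairing, and in the movement text as the definition of matched. Make sure the automated movement routine draws only from these pairs.

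The cost is a restriction in the surrogate code and no new data. There are fewer eligible pairs: with order balanced evenly, 75 couples share a position and instruction, so each sharer has 74 eligible supporters instead of 1,192 series. That is still many per real dyad.
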